#### **2.3.5.5 Assessment of the soccer players**

A number of musculoskeletal assessments will be conducted in order to establish intrinsic risk factors for injuries (Maffey & Emery, 2006; Brumitt et al., 2013; Bahr & Krosshaug, 2005). A number of assessment techniques will be performed to identify weakness, limitation, or impairment that could be associated with the occurrence of injuries. The assessment techniques include the anthropometric assessment, the range of motion and flexibility of muscles, the specific neural mobility tests, stability, strength as well as proprioception testing. Due to minimal resources, equipment and time, on-field testing will be performed. The field will be set up in a circuit form where each circuit will be monitored by the research team members. Each station will have the description of the procedure to ensure that all the steps are followed and all the subjects are undergoing the same amount of difficulties. Though the research assistants will be trained about the measurements, three readings will be used and average will be recorded or as directed by the test protocol. Each test and measurements are described in the appendix E.

### **2.3.6 Procedure**

#### **2.3.6.1 Data collection**

Ethical approval for the study will be sought from the University of Cape Town. Permission to conduct the study will be requested from the ministry of sports and culture, and FERWAFA. Finally, permission will be sought from the teams in the first and second division. Written consent will be obtained from the coaches and players from both divisions as well as for the parents or legal guardians of under 18 players (Appendices F, G, H, I).

Physiotherapists with Bachelor's degree will be recruited as research assistants. Training will be conducted where they will be informed about the research aims, objectives and the significance of the study. They will be trained about the methods of data collection of the study. They will be taught about the ethical considerations as well as their role in the study. They will further be familiarized with the tools that will be used for data collection to ensure reliability and standardization among the data collectors. The training will be done using the guidelines for collecting data in studies of soccer developed by the FIFA (Fuller et al., 2006) and the UEFA (Hägglund, Waldén, Bahr, & Ekstrand, 2005). The training will be conducted in a youth team that will not participate in the main study. Discussions and consultations among the research team members will be organized to ensure common understanding and performance of the measurement and recordings. They will also be trained on the standardized way of communicating with coaches and medical personnel regarding questions that may be asked.

Coaches and assistant coaches of the teams in the first and second division will be approached by the researcher where they will be explained the aims, objectives, rationale and procedure for the study. Further appointments will be organized for more explanation and opportunity to ask any questions pertaining to the study. Verbal explanations will be provided to the coaches in addition to the participant information sheet requesting them to participate in the study. Henceforth written consent will be sought from the coaches signing the consent form. This will be done during the preseason period.

The coaches will be requested to allocate time that will be convenient for them and the players to perform the measurement and test pertaining to the study.

Player exposure forms will then be provided to the coaches and will be requested to record every training time that each player participate in soccer activities. Because coaches are focusing on the game during the match, it could be hectic for them to record match exposure. For this reason, match exposure will be obtained from the reports that are submitted by the referee to the FERWAFA.

Before the beginning of each season the FERWAFA set a deadline for the teams to submit the list of all the players that they will use in the league. Therefore the list of all the players will be obtained from the FERWAFA while additional information pertaining to the study will be requested from the team management.

All the medical personnel of the teams will be invited into the briefing meeting that will be held at the FERWAFA premises to explain to them about the study and their task in the study. They will be explained how to fill the injury report forms and they will be asked to report any injury that will take place during data collection. The injury report and exposure forms will be collected by the researcher or the research assistants after every two weeks.

Training and match exposure as well as injury recording for the main study will commence one week before the first game because training performed during that week is for the preparation of the first game. The first division season will start in September 2014 while the second division season will start in November 2014. The exact dates will be obtained from the FERWAFA after the general assembly meeting preparing the league that will take place after the season 2013-2014. Data collection will take place throughout the season up to the last game. Because the FERWAFA allows the teams to recruit new players during the mid season, players who will join the teams halfway through will be recorded from the period recruited. The season will end in June 2015 for the first division and May 2015 for the second division. At the end of the season, the last two teams from the first division are relegated to the second division while the first two teams in the second division are promoted to the first division. A period of rest is given to the

teams and players at the end of the season 2014-2015 which allows teams to reorganize and recruit new players. Changes that will take place during this period will be noted and appropriate actions will be done to allow the injury surveillance to continue in the subsequent season. The study two with intervention will commence at the beginning of the season 2015-2016.

Figure 2: Study one framework

[figure not shown]

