### **2.3.4 Participants**

The Federation of Rwandese Football Association (FERWAFA) organizes tournaments at different levels. The top flight male first division is composed of 14 teams while 19 clubs compete in the second division.

The first division competition is the country's primary soccer competition. There are 14 men's association soccer clubs that participate in the league and it operate on the process of promotion and relegation. The teams play 26 matches, where each club plays the others twice, during the season which runs from September to June. The total number of matches is 364 matches. The league is currently sponsored by the largest brewer and soft beverage company in Rwanda on its band new beer named "turbo king" and thus officially known as "turbo king national football league". At the end of the completion, the teams are ranked according to the total points accumulated during the season. In case of equal number of points the goal calculation of the number of goals scored and conceded come in favor of the team to determine the winner. The

league winner qualifies to represent the country in the CAF champions' league while the two lowest placed teams are relegated into the second division. Many teams in the first division are sponsored either by private business companies or government institutions (for example, the police, the army and other governmental parastatals) (FERWAFA, 2008).

There are 19 teams competing in the second division organized by the FERWAFA. Unlike the first division, the second division teams do not play each other because each team would play 36 games. Playing many games require many resources from the teams, the organizing federation as well as a longer period of time. Therefore the teams are randomly divided into two groups. Group A composed of 10 teams and group B composed of 9 teams. Teams in each group play each other and accumulate the points according to the win or draw rules. The first two teams in each group qualify to the semifinal stage where they play the teams from the other group. The winners of the semifinal stage qualify to the final and are automatically promoted to the first division. The competition ends while the teams play between 11 and 12 matches. The second division season runs from November to May. The FERWAFA requires each team to register maximum 30 players; therefore the maximum number of players that will participate in this study are 990.

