### **Inclusion criteria**

Players who will be having contracts with the teams will be included in this study. Prior to the start of the league players undergo a medical assessment to be cleared and issued a playing license. Therefore, players having a valid license to participate in the league from the FERWAFA will be included. Players presenting injury at the beginning of the study will be included when cleared to join teams' training and matches. Data from players who will be selected to participate in the national team will also be included in the study.

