### **2.3.5.3 Exposure form**

A specific player exposure form developed by FIFA will be used to record detailed information regarding player involvement in soccer (Fuller et al., 2006) (Appendix C). The forms will be given to the coaches to record duration of the training sessions. Match exposure will be gathered from the referees' reports submitted to FERWAFA. Any form of physical activities supervised by the coach that the players will undertake during training will be recorded as training exposure time. Match exposure time is defined as the amount of time the player will be involved while the team is playing against another team. The duration of the training will be recorded from the start of the warm up to the end of the cool down session (Parry & Drust, 2006). Exposure form will also record player absence from training and competition and the reason for this absence. The forms will be collected by the research team once in two weeks.

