### **2.3.5.4 Injury registration form**

Similar to the exposure form, an injury report form (Appendix D) will be used to collect data pertaining to the incidence of injuries by the team medical personnel or the research assistant for

the teams that do not have any medical personnel (Fuller et al., 2006). The form is comprehensive and designed in such a way that the injuries are recorded on the front side of the page while all the definitions pertaining to the type, anatomical location, severity and circumstance of injury are provided at the back page of the form. The form has been developed and used during major FIFA tournaments and Olympic games (Junge, 2004) and has been extensively used in other studies (Junge et al., 2011) but is not routinely used in soccer in Rwanda. For example an injury is defined as any physical complaint that resulted from soccer participation whether in training or match. It does not necessarily mean that there is a need or not of medical attention.

A meeting with the team medical personnel will be organized to explain to them about the purpose of the study and their role in the study. They will be given the report forms to record any injury that will happen during the time of the study. Further explanations will be given to them as to specific definitions and the way of recording.

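### Match injuries and match hours are not defined over the same matches, so match incidence may be overstated, by an amount that may differ between divisions

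*Combined protocol and SAP*

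**What the plan says.** Section 2.3.6.1 explains that coaches are too occupied during a game to log match time, and therefore "match exposure will be obtained from the reports that are submitted by the referee to the FERWAFA". Coaches' records cover training time, and no other source of match minutes is named.

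The definition in 2.3.5.3 is wider than that source need be: "Match exposure time is defined as the amount of time the player will be involved while the team is playing against another team". It is not confined to league fixtures. The injury definition in 2.3.5.4 is equally open: "an injury is defined as any physical complaint that resulted from soccer participation whether in training or match". Of the team medical personnel, 2.3.6.1 says that "they will be asked to report any injury that will take place during data collection". The inclusion criteria under 2.3.4 add: "Data from players who will be selected to participate in the national team will also be included in the study". Sections 2.1 and 2.3.4 also show that non-league matches exist, through tournaments run by continental and world bodies and the continental entry of the first-division champion.

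Section 2.3.9 computes incidence as injuries times 1000 over exposure hours, for match, training or both, and compares groups by z-statistics and rate ratios. Section 2.4.7.1 keeps the same data collection for season two, and 2.4.8 applies the same incidence analysis to the two study groups and the two divisions. No sentence ties a counted match injury to a match whose hours were captured.

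**The concern.** An incidence rate is interpretable only if the events arise in the person-time that is counted. Here the events can come from any match, but the match time comes only from matches for which a referee reported to the federation. A counted match without a report adds to the numerator alone.

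The rates at stake serve the objectives in 2.3.2: the comparison of divisions, and the injury pattern in training against matches. Missing match hours would overstate the match rate and the overall rate, and would widen the match-versus-training contrast. Because the two divisions play very different numbers of league matches, the same number of unreported games would not cancel out of their rate ratio.

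**Working it through.** **Inputs.** All are from 2.3.4 unless noted.

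- First division: "The teams play 26 matches, where each club plays the others twice, during the season which runs from September to June".
- Second division: "The competition ends while the teams play between 11 and 12 matches", and "The second division season runs from November to May". Teams are in groups of 10 and 9.
- F, the number of matches per team whose injuries count but whose hours are in no referee report: not given, so assumed.

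**Reproducing the match counts.** First division: 2 × 13 = 26, as stated. Second division: a single round robin gives 9 or 8 matches. If a two-leg semifinal and a final add 3, the totals are 12 and 11. The stated 11–12 is thus reproduced for finalists, on that assumption about the format. I use the stated 11–12 and show other values below.

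**Formula.** With the same injury rate per hour and equal match length in reported and unreported matches, match incidence is inflated by 1 + F/M. The false second-to-first rate ratio is (1 + F₂/M₂)/(1 + F₁/M₁).

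**Equal F in both divisions.**

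| F | First (M = 26) | Second (M = 12 to 11) | False ratio |
|---|---|---|---|
| 1 | 1.04 | 1.08–1.09 | 1.04–1.05 |
| 2 | 1.08 | 1.17–1.18 | 1.08–1.10 |
| 4 | 1.15 | 1.33–1.36 | 1.16–1.18 |

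For example, at F = 4: 1 + 4/26 = 1.154, 1 + 4/12 = 1.333 and 1 + 4/11 = 1.364. The ratios are 1.333/1.154 = 1.16 and 1.364/1.154 = 1.18.

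**Sensitivity to M₂.** At F = 4, the ratio is 1.25–1.30 if most second-division teams play only 9 or 8 matches. It is 1.06–1.08 if group play were a double round robin of 18 or 16.

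**Unequal F.** The second division is inflated more only if F₁/F₂ is below M₁/M₂, which is 26/12 = 2.17 to 26/11 = 2.36.

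- If F follows season length (10 against 7 months, ratio 1.43) at 0.5 matches a month, the factors are 1 + 5/26 = 1.19 and 1 + 3.5/12 to 1 + 3.5/11 = 1.29–1.32. The second division is inflated more.
- If F₁ = 6 and F₂ = 2, they are 1.23 and 1.17–1.18. The direction reverses.
- If F₂ = 0, only the first division is inflated.

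**National-team games alone.** Assume 4 to 8 matches of 1.5 hours, filled wholly by first-division players: 4 × 11 × 1.5 = 66 to 8 × 11 × 1.5 = 132 player-hours. First-division league hours are 14 × 26 = 364 team appearances × 16.5 = 6,006. The shortfall is 1.1–2.2%, so a large bias would need unreported club matches.

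**Overall rate.** Its factor is smaller than 1 + F/M, because training hours enlarge the denominator. The plan gives no training hours, so I do not quantify it. If a coach entered a friendly as training time, the training rate would fall and the match-versus-training contrast would be distorted further.

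**The case against.** The strongest reply is that the mismatch may be small or absent. Nothing limits the referee reports to league games, so friendlies may be covered. Recording starts only a week ahead of the opening fixture and stops at the last one, so most preseason friendlies add neither injuries nor hours. The sentence on national-team players may simply keep them in the cohort, and no one is named to report injuries from those games. Appendices C and D are not in the text available, so their fields cannot be checked. All of this stands: it makes the bias a risk of unknown size. It does not supply the missing rule.

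A reader might infer that second-division incidence is certain to be inflated more, because that division plays fewer matches. The documents do not support this. It needs roughly equal numbers of unreported matches per team, and the only non-league club matches that the documents tie to a division are the first-division champion's continental games. No section says which division supplies national-team players.

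A reader might also infer that the randomised comparison is biased. Both arms are second-division teams allocated at random, and the documents give no reason for unreported matches to differ by arm. Only such a difference would matter.

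**Conclusion.** The point holds in a conditional form. Match hours have a single source, match injuries have no corresponding limit, and nothing pairs them. If any counted match lacks a referee report, match incidence is too high by 1 + F/M, the overall rate by less, and the match-versus-training contrast is distorted.

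For an assumed equal F of 2 to 4, the overstatement is 8–15% in the first division and 17–36% in the second, with a spurious rate ratio between them of about 1.08 to 1.18. These figures rest on the assumed F, on an equal injury rate per hour in reported and unreported matches, and on the stated 11–12 second-division matches. Neither the occurrence of inflation nor its direction by division is established. This is a cheap improvement and does not undermine the design.

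**What to change.** In 2.3.9 and 2.4.8, state that the match rate and the overall rate count a match injury only if it was sustained in a match whose hours were captured from a referee report. List injuries from all other matches separately. This sets the factor to 1.00 in both divisions whatever F is. Time in those other matches should likewise not be entered as training.

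Two clarifications belong with the rule: which matches the federation's reports cover, and how a complaint of gradual onset is assigned to a match, to training or to neither.

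The cost is one analysis rule. The downside is that a few injuries leave the headline rates, although they remain visible in the separate listing. Asking coaches to record the missing match minutes is not needed for this, and it would run against the reason 2.3.6.1 gives for sparing them that task.

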Appendix H: INFORMATION SHEET FOR PLAYERS' PARENTS OR LEGAL GUARDIANS

Appendix I: INFORMED CONSENT FORM

Appendix J: DATA ANALYSIS TABLE

Appendix K: QUESTIONNAIRE FOR COACHES

Appendix L: 11+ WARM UP EXERCISES

Appendix M: CONTENT FOR THE TRAINING

Appendix N: THE "11+" RECORDING FORM

## GLOSSARY OF TERMS

**Coach:** One who instructs players in the fundamentals of a competitive sport and directs team strategy (Merriam-Webster Online Dictionary, 2010).

**Exposure factor:** Individual participation time recorded (Hägglund, Waldén, & Ekstrand, 2006)

**Recurrent injury:** injury of the same type and at the same site which occurs after a player's return to full participation within two months (Fuller et al., 2006).

**Injury prevention:** the implementation of interventions to eliminate or reduce the likelihood and the severity of injuries caused by external or internal mechanisms before they occur (Lawrence, 2008).

**Injury severity:** Based on absence from game or practice participation: slight (1–3 days), minor (4–7 days), moderate (8–28 days), major (>28 days) (Fuller et al., 2006).

**Rehabilitation:** A player is considered injured until given clearance by medical staff to participate fully in team training and match play (Hägglund et al., 2006).

**Soccer Injury:** Any physical complaint resulted for soccer participation whether in training or match (Junge & Dvorac, 2000).

**Training session:** Coach directed physical activities (on field, gym, recovery sessions, aerobics) carried out with the team (Hägglund et al., 2006).

**Readiness for injury prevention:** Coach related factor that is assumed to influence sports injury outcomes (Siwon, 2013).

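### Recording stops at the last game, so severity is truncated for injuries still open then, and none starting in the last 28 days can be classed as major

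*Combined protocol and SAP*

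**What the plan says.** Section 2.3.6.1 starts recording one week before the first game and gives its end as follows: "Data collection will take place throughout the season up to the last game". Teams then rest. The section promises unspecified steps so that surveillance can carry on in the next season, but describes no collection during the break. After season two, the only later step in section 2.4.7.1 is a questionnaire for coaches.

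The glossary grades severity by absence from games or practice: "slight (1–3 days), minor (4–7 days), moderate (8–28 days), major (>28 days". It also says when an injury ends: "A player is considered injured until given clearance by medical staff to participate fully in team training and match play". The exposure form in section 2.3.5.3 records absences, but only while forms are being collected.

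The two divisions have different calendars. In section 2.3.4 the first division plays from September to June, and "The second division season runs from November to May". Objective (a), in sections 1.3 and 2.3.2, compares severity between the divisions. Section 2.3.9 tests severity with a chi-square or Fisher's exact test.

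On what counts as an injury, section 2.3.5.4 says that "an injury is defined as any physical complaint that resulted from soccer participation whether in training or match", and adds: "It does not necessarily mean that there is a need or not of medical attention". It also says that severity definitions are printed on the back of the injury form (Appendix D).

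**The concern.** A severity grade based on days lost needs a return date. If recording stops while a player is still out, only the days up to the last game are known, and the injury may be placed in a lower band than it belongs in. The top band cannot be reached at all by an injury that starts in the last 28 days. The same 28 days are a larger share of the shorter second-division season, so the loss is not equal between the groups that objective (a) compares. Return dates that are not collected soon after the season may be hard to recover, and no later analysis can restore them.

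A smaller point concerns the bottom of the scale. Any physical complaint is an injury, but the glossary bands begin at one day of absence. A complaint with no time lost counts towards incidence and has no band in the glossary.

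**Working it through.** The plan states no figure on this point, so there is nothing to reproduce. The check asks how large the truncated part of each season is, and what it does to the comparison.

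**Inputs.** The major band is more than 28 days (glossary). Recording starts 7 days before the first game and ends at the last game (section 2.3.6.1). Season one runs from September 2014 to June 2015 in the first division and from November 2014 to May 2015 in the second. Exact days are not given, so the earliest and latest dates within those months set the range.

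**Step 1: recorded season length.** L = days from first to last game, both included, plus 7.
- First division: 252 days (30 September to 1 June) to 310 days (1 September to 30 June); mid-month dates give 281.
- Second division: 160 days (30 November to 1 May) to 219 days (1 November to 31 May); mid-month dates give 189.

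**Step 2: share of truly major injuries that cannot be classed as major.** With even spread over the season, f = 28 / L.
- First division: 28/310 = 9.0% to 28/252 = 11.1%; mid-month 28/281 = 10.0%.
- Second division: 28/219 = 12.8% to 28/160 = 17.5%; mid-month 28/189 = 14.8%.

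The ranges do not overlap, so the second division loses the larger share on any dates the stated months allow.

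**Step 3: effect on the division comparison.** Let the true major share be m in both divisions (m is an assumption; the documents give no severity mix). If truncated injuries stay in the denominator under a lower band, the observed share is m(1 − f). The spurious gap is m(f2 − f1), where 1 and 2 denote the divisions.

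| Dates (first / second division, days) | f2 − f1 | m = 5% | m = 15% | m = 30% |
|---|---|---|---|---|
| Full months (310 / 219) | 3.8 points | 0.2 | 0.6 | 1.1 |
| Mid-month (281 / 189) | 4.9 points | 0.2 | 0.7 | 1.5 |
| Widest contrast (310 / 160) | 8.5 points | 0.4 | 1.3 | 2.5 |
| Narrowest contrast (252 / 219) | 1.7 points | 0.1 | 0.3 | 0.5 |

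The gaps are in percentage points. Nine of the twelve lie between about 0.2 and 1.3. As an example, with full months and m = 15%, the observed shares are 15 × (1 − 0.090) = 13.6% in the first division and 15 × (1 − 0.128) = 13.1% in the second. Each is below 15%, but they differ little.

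**Step 4: how many injuries need a closing date.** Take assumed mean absences of 2, 5.5 and 18 days for the first three bands, and count major injuries only over their last 28 days (earlier ones have already been classed). The share of all injuries with an unsettled band at the last game is the mix-weighted mean divided by L. For assumed slight/minor/moderate/major mixes from 50/25/20/5 (mean 7.375 days) to 15/20/35/30 (mean 16.1 days), this is 2.4–6.4% in the first division (7.375/310 to 16.1/252) and 3.4–10.1% in the second (7.375/219 to 16.1/160).

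**Step 5: would the next season recover the dates?** If season two keeps the same months, the gap before recording resumes is 56–114 days in the first division and 147–206 in the second. A player seen training again after that gap has no recorded return date, and no further recording is described after season two.

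**The case against.** The strongest reply is that the effect on the planned comparison is slight. Most long absences begin early enough to be scored in full, and the gap between divisions in Step 3 is about a point or less in most cases. The text also does not forbid closing an open record later: the glossary treats a player as injured until cleared, and section 2.3.6.1 says that changes during the break will be noted. The size argument stands. The argument from silence does not amount to a follow-up rule, and it offers nothing after season two.

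Three stronger readings are tempting, and the documents do not support them.

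- *Severity cannot be scored at either end.* At the upper end this is true only of injuries still open at the last game. At the lower end, the missing zero-day band is shown only for the glossary. Appendix D is said to carry severity definitions and was not available to us. It may contain a zero-day band or a field for expected absence.
- *Re-injury is understated, more so in the second division.* A recurrence must follow "return to full participation within two months", and a 61-day window would be incomplete for 19.7–24.2% of returns in the first division (61/310 to 61/252) and 27.9–38.1% in the second (61/219 to 61/160). But section 1.3 plans an incidence of re-injuries, and section 2.3.9 expresses incidence per 1000 playing hours. During the rest period few team hours and few soccer injuries accrue, so numerator and denominator are lost together. Those percentages measure incomplete windows and are not the bias in a rate. The re-injury objective compares teams by medical support rather than by division, and section 2.3.2 replaces it with a description of that support.
- *The trial result is biased.* Both randomised arms are second-division teams on one calendar, so truncation should be similar between them.

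**Conclusion.** The concern holds in a limited form. As written, the plan truncates the absence of every injury open at the last game and rules out the major band for injuries starting in the last 28 days. That affects 9.0–11.1% of truly major injuries in the first division and 12.8–17.5% in the second, so the major share is understated in both. The distortion of objective (a) is small: mostly about 0.2–1.3 percentage points, and at most 2.5 when a 30% major share meets the dates that separate the divisions most.

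These figures assume that injuries are spread evenly over the season, that the true major share is the same in both divisions and lies between 5% and 30%, and that truncated injuries are kept under a lower band. If open injuries were dropped instead, the size would differ. The point is worth acting on because the remedy is cheap and the missing dates may be beyond recovery later. It does not threaten the randomised comparison. The lower-end point is a matter of reconciling the glossary with Appendix D.

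**What to change.** 1. In section 2.3.6.1, state that for each injury open at the team's last game, the existing research assistant or team contact records the date the player is next fit for full training. If that date cannot be obtained, code the injury as unresolved at season end with its minimum days of absence, rather than placing it in a lower band. Apply this at the end of both seasons, and report the unresolved injuries as their own row in the severity tables.
2. Reconcile the glossary severity scale with the definitions in Appendix D. If neither has a zero-day category, add one, because any physical complaint counts as an injury.
3. Keep re-injury as a rate per 1000 hours, as planned. If a re-injury proportion is also reported, restrict it to injuries with a full two-month observed window.

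The cost is some wording on the form and in the glossary, a short contact for each open injury (roughly 2–10% of injuries under the assumed mixes), a short delay in closing the data, and some injuries reported as unresolved. Design, sample and intervention are unchanged.
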